## Abstract

**Background:**

Evidence supports the use of exercise for chronic low back pain (CLBP); however, adherence is often poor due to ongoing pain. Auricular acupuncture is a form of pain relief involving the stimulation of points on the outer ear corresponding with specific body parts. It may be a useful adjunct to exercise in managing CLBP; however, there is only limited evidence to support its use with this patient group.

**Methods/Design:**

This study was designed to test the feasibility of an assessor-blind randomised controlled trial which assess the effects on clinical outcomes and exercise adherence of adding manual auricular acupuncture to a personalised and supervised exercise programme (PEP) for CLBP. No sample size calculation has been carried out as this study aims to identify CLBP referral rates within the catchment area of the study site. The researchers aim to recruit four cohorts of n = 20 participants to facilitate a power analysis for a future randomised controlled trial. A computer generated random allocation sequence will be prepared centrally and used to allocate participants by cohort to one of the following interventions: 1) six weeks of PEP *plus *manual auricular acupuncture; 2) six weeks of PEP alone. Both groups will also complete a further six weeks of self-paced exercise with telephone follow-up support. In addition to a baseline and exit questionnaire at the beginning and end of the study, the following outcomes will be collected at baseline, and after 7, 13 and 25 weeks: pain frequency and bothersomeness, back-specific function, objective assessment and recall of physical activity, use of analgesia, perceived self-efficacy, fear avoidance beliefs, and beliefs about the consequences of back pain. Since this is a feasibility study, significance tests will not be presented, and treatment effects will be represented by point estimates and confidence intervals. For each outcome variable, analysis of covariance will be performed on the data, conditioning on the baseline value.

**Discussion:**

The results of this study investigating the adjuvant effects of auricular acupuncture to exercise in managing CLBP will be used to inform the design of a future multi-centre randomised controlled trial.

**Trial Registration:**

Current Controlled Trials ISRCTN94142364.

## Background

Current research evidence supports the use of exercise-based treatment programmes for CLBP that encourage the patient to assume an active role in their recovery [1-3]. Outcomes are also claimed to improve when exercise is supervised and personalised/individually tailored [1,3-5]. One of the main factors limiting the success of such an active approach is the patient's level of adherence, which often suffers as a result of exercise-induced exacerbations in pain [2,3,5,6]. People with CLBP typically lack faith in the recommendation to stay active *despite *pain [7], with the result being an avoidance of activity in order to avoid pain. The results of a recent prospective cohort study [8] have indicated that people with CLBP who experienced a reduction in pain during treatment also experienced the greatest functional improvements. The benefits of adequate pain control may be expected to contribute to the effectiveness of exercise-based intervention, by increasing levels of activity and self-confidence, and modifying pain perception and disability [5]; thus there is the potential for an adjunctive pain relieving modality for exercise therapy.

Of the various complementary and alternative medicine (CAM) available for pain relief, acupuncture has become increasingly accepted as an effective means of pain control, due to its holistic approach and limited side effects [9,10]. Current evidence supports the use of acupuncture for people with CLBP, particularly when provided alongside other conventional therapies [10-13]. Thomas and colleagues [13] concluded that acupuncture was significantly more effective in reducing bodily pain and participants' concerns about back pain than usual care for up to 24 months. A recent study has suggested that stimulation of auricular (ear) acupuncture points is effective for the treatment of CLBP [14]: this study compared electrical stimulation of auricular points with manual stimulation, and found that both groups experienced pain relief. Aside from the above study and the use of auricular acupuncture for pain relief for cervical spine pain [15,16] and after knee and hip surgery [17,18], the evidence for auricular acupuncture is limited and there have been no studies that have examined the adjuvant effect of auricular acupuncture to an exercise programme in CLBP. Auricular acupuncture is relatively easy to administer, promoting pain relief with minimal interruption to the individual's normal daily activities. Needles can stay *in situ *for up to seven days allowing participants to self-treat at home. It is proposed that the addition of AA to a supervised PEP will address the pain relieving expectations of participants, and help to decrease the barriers to exercise that can often limit adherence. The individually tailored approach to exercise is intended to foster the development of active self-management strategies, and functionally-related goals that are the necessary pre-requisites for effective long-term symptom management.

The aim of this study is to evaluate the feasibility of a randomised controlled trial (RCT) exploring the effects on clinical outcomes and exercise adherence of adding manual AA to a PEP, when compared to the PEP alone, for participants with CLBP using the MRC framework for the design and evaluation of complex interventions [19].

## Methods/Design

### Study design

An assessor-blind randomised controlled trial with six-month follow-up. Ethical approval was obtained from the Northern Ireland Office for Research Ethics Committee.

### Participants

Individuals diagnosed with CLBP who fulfil the inclusion/exclusion criteria (see Table 1) will be recruited between April 2007 and September 2008 to attend classes in a purpose built gym at the University of Ulster, Jordanstown, Northern Ireland. Several approaches to recruitment will be undertaken, via healthcare professionals and via the general public. Prospective and retrospective recruitment from General Practitioner (GP) practices (n = 14) within the catchment area of the University of Ulster, plus identification of people with CLBP from the physiotherapy waiting lists (referral via GP) in a large Healthcare Trust, close to the University, will be used. GPs willing to participate will receive a full explanation (verbal and written) of the trial procedure, following which their agreement to participate will be confirmed in writing. The physiotherapy managers of local primary care trusts, typically receiving GP referrals for CLBP, will also receive a full explanation (verbal and written) of the intended trial dates and procedures. Finally, the feasibility of recruitment from the general public, and appropriateness of referrals via this route, will be tested via poster/email advertisements and a website [20] to staff and students at the University of Ulster. For this method of recruitment, the relevant GP's contact details, supplied by staff and students, will be used to confirm the medical suitability of each participant for our trial.

**Table 1 T1:** Inclusion/exclusion criteria

**Inclusion criteria**	**Exclusion criteria**
Participants with chronic (≥3 months) or recurrent (≥3 episodes in previous 12 months) LBP of mechanical origin with/without radiation to the lower limb	Currently or having received treatment for CLBP within the previous 3 months
Males/females between 18–65 years	Red flags indicating serious spinal pathology, e.g. cancer, cauda equina lesion
No spinal surgery within the previous 12 months	Radicular pain indicative of nerve root compression **
Participants deemed suitable by their GP to carry out an exercise programme	Participants diagnosed with severe spinal stenosis, spondylolisthesis, fibromyalgia
Participants deemed suitable by their GP to receive acupuncture treatment	History of systemic/inflammatory disease, e.g. rheumatoid arthritis
Participants willing to attend for a 6-week treatment programme of exercise and manual AA	Concomitant medical condition that contraindicates acupuncture
Fluency in English (verbal and written)	Participants with acute (< 6 weeks) or subacute LBP (6–12 weeks), provided that they have experienced < 3 LBP episodes during the previous 12 months
Access to a telephone (for follow-up support)	Previously received auricular acupuncture
Participants categorised as 'low' or 'moderate' activity levels on the International Physical Activity Questionnaire (IPAQ)	Participants with any confounding conditions such as a neurological disorder or currently receiving treatment for cancer
	Road traffic accident causing LBP
	History of psychological or psychiatric illness
	Participants having multiple body and/or ear piercings
	Fear of needles

** In accordance with the Clinical Standards Advisory Group (1994) [21] and the Royal College of General Practitioners Guidelines (Waddell et al., 1999) [22], participants presenting with any or all of the following criteria indicative of radicular pain will be excluded from the study:

(a) unilateral pain usually worse than back pain;

(b) pain generally radiating to the foot or toes;

(c) numbness or paraesthesia in the same distribution;

(d) reduced straight leg raise that produces leg pain;

(e) motor, sensory or reflex change limited to one nerve root.

For all methods of recruitment, once we receive confirmation that they are medically fit to participate in the trial, participants will receive a trial information pack from the lead researcher, be screened by phone, and if eligible an appointment will be made for baseline assessment one week later. During this appointment, the trial procedures will be explained in detail and written informed consent will be obtained. Participants who provide written informed consent will then be randomised, by cohort, according to Figure 1. In order to investigate whether treatment preference has any influence on outcomes, prior to randomisation each participant will be asked which treatment (A or B) he/she would prefer to receive.

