### Aim and Objectives

To evaluate the feasibility of an RCT exploring the effects on clinical outcomes and exercise adherence of adding manual AA to an individually tailored and supervised exercise programme, when compared to the exercise programme alone.

To determine the feasibility of the trial procedures and establish the most efficient and effective design for a larger RCT by:

(i) Identifying the rate of participation and referrals from the various recruitment routes;

(ii) Determining the actual numbers recruited, adherence and drop out;

(iii) Piloting the methodological procedures;

(iv) Identifying participants' use of a free telephone advice and support service;

(v) Completing a qualitative exploration of the trial procedures and design;

(vi) Confirming training and monitoring requirements for a main trial; and,

(vii) Identifying a crude approximation of the effect size of each treatment package.

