### Sample size

No sample size calculation has been carried out as this study aims to identify the referral rates of CLBP participants within the catchment area of the study site. Recruitment will be on a consecutive basis from participating practices, physiotherapy waiting lists and the general public, and will enable the researchers to estimate expected recruitment rates from each of these sources for the main RCT. The researchers aim to enrol eight cohorts of participants, each containing a maximum of n = 10 participants (total n = 80 participants), with randomisation to treatment taking place by cohort. Based on the results of previous trials investigating exercise or acupuncture for LBP, a 30% drop-out rate is anticipated between the beginning of treatment and the follow-up, so it is anticipated that n = 56 participants will complete the trial. The trial statistician is satisfied that this sample size will be sufficient to refine the study protocol, perform a power analysis, and establish the number of participants needed for the main RCT.

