### Statistical methods

Since this is a feasibility study, significance tests will not be performed or reported, and treatment effects will be represented by point estimates and confidence intervals. For each outcome variable ANCOVA will be performed on the data, conditioning on the baseline value. Trends over time and time-by-treatment interactions will be explored using repeated measures ANOVA. The influence of treatment preference on outcomes will also be explored. For all analyses, the residuals will be examined for evidence of non-normality. If substantial evidence of non-normality is found, appropriate alternative (non-parametric) tests will be applied, and specified as the primary analysis method in the main study. The cluster randomised nature of the design will be accounted for in the analysis by fitting a mixed effects model. Monthly recruitment rates and ratio of number screened: number enrolled will be tabulated. This information will be used to help select the recruitment period and number of centres for the main RCT. The assessment of participant satisfaction will be tabulated, as will any recorded difficulties experienced by the participants or therapists. This information may be used to modify the interventions used in the main RCT. If analgesic use differs substantially between the two groups, consideration will be given to using this as a primary outcome variable in the main RCT.

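### The general-public recruitment route is advertised only to staff and students of the host university, so its rate and eligibility fraction do not estimate those of the general public for the main RCT

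*Protocol article*

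**What the plan says.** The Participants section of the protocol article divides recruitment into two kinds: "Several approaches to recruitment will be undertaken, via healthcare professionals and via the general public". The first kind covers 14 GP practices and the physiotherapy waiting lists of a nearby Trust. The second is introduced as a test of "the feasibility of recruitment from the general public, and appropriateness of referrals via this route", and the same sentence says how this "will be tested via poster/email advertisements and a website [20] to staff and students at the University of Ulster". The next sentence confirms the audience: for this method, "the relevant GP's contact details, supplied by staff and students, will be used to confirm the medical suitability of each participant".

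Three later places rely on this route:

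- Aim and Objectives, item (i): "Identifying the rate of participation and referrals from the various recruitment routes".
- Sample size: "Recruitment will be on a consecutive basis from participating practices, physiotherapy waiting lists and the general public", which "will enable the researchers to estimate expected recruitment rates from each of these sources for the main RCT".
- Statistical methods, on the monthly recruitment rates and the ratio of screened to enrolled: "This information will be used to help select the recruitment period and number of centres for the main RCT".

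The Discussion paragraph of the Abstract says the main trial is to be multi-centre.

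**The concern.** The route carries the name of one population and samples another. Nothing in the article describes advertising beyond the university, or how a respondent from outside it would be handled. If the plan is followed as written, the figure reported as the general-public recruitment rate will be the rate among people who belong to the institution running the trial. They can be reached through internal email and posters and have a standing tie to the host. A centre in the main trial may have no such population.

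Recruitment by route is a stated objective of this feasibility study, and its recruitment data are meant to help set the recruitment period and number of centres. If the campus figure is carried forward under the general-public name, planners will be relying on a source that was never tried. The same applies to the appropriateness of referrals: the share of advertised respondents who prove eligible is a property of the group that saw the advertisement.

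**Working it through.** The point is not numerical, so the main check sets the statements side by side.

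**Step 1. The one related figure that can be reproduced.** The Sample size section gives eight cohorts of at most 10 and a 30% drop-out: 8 × 10 = 80, and 80 × (1 − 0.30) = 56. This matches the stated 56 completers. It contains nothing specific to a route, so it neither supports nor weakens the point.

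**Step 2. Named population against approached population.**

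| Place in the protocol article | Population named | Population approached |
|---|---|---|
| Participants, two kinds of approach | General public | Not yet stated |
| Participants, advertising sentence | General public | University staff and students |
| Participants, GP confirmation sentence | This method of recruitment | Staff and students supply the GP details |
| Sample size, list of sources | General public | No new channel described |

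The restriction is stated twice, in consecutive sentences, so it is not a slip of phrasing. No other section widens it.

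**Step 3. What is inferred from the route.** The Participants section promises two things: feasibility of recruitment, and appropriateness of referrals. The Sample size section promises a third, an expected recruitment rate for each source for use in the main RCT. The explicit promise for the main trial concerns the rate. Appropriateness is promised only as something this route will test.

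**Step 4. Does the inference follow?** A recruitment rate depends on who is exposed to the advertisement, by what channel, and how easily they can attend. Here the exposed group is one institution's staff and students, the channels include internal ones, and the treatment gym belongs to the same university. None of these need hold for the public around another centre. The observed rate and eligibility fraction are valid for a university self-referral route and do not estimate the general-public quantities.

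**Step 5. Can the error be sized?** This would need the expected or observed number enrolled by this route, the number exposed, and a corresponding figure for a community route. The article gives none of them, so no rate for this route can be computed before or after a fix.

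**The case against.** The strongest reply is that this is a matter of labelling. The Participants section contrasts referral by professionals with advertised self-referral, and calls the second kind the general public as shorthand. It names the audience openly, so a careful planner would know who was approached. The route also does useful work: it pilots advertising, self-referral and the extra step of confirming suitability with the GP. And the Sample size section already promises rates from each source, so a campus rate would be visible and could be set aside.

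Much of this stands. The data are not useless, and reporting by source is already implied for recruitment rates. It does not remove the point, because the Sample size section repeats the label without the qualification and attaches an inference for the main RCT to it. Figure 1 and the recruitment website are not available here. They might show a wider reach, but they would not change what the text says.

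Several stronger readings are tempting, and the document does not support them:

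- *A numerical delay to the main trial.* One could divide 80 by the 18 recruitment months (April 2007 to September 2008), giving 80/18 = 4.4 per month, assume that a share s came from the campus, and conclude that recruitment elsewhere takes 1/(1 − s) times as long. No value of s is given, 80 is a ceiling, and the plan nowhere says the main trial will assume that rate at each centre. The result only restates the assumption.
- *Inflation by pooling.* The Statistical methods section does not say its tables are split by route, but nothing there overrides the by-source promise in the Sample size section.
- *Younger participants with better attendance.* Neither is documented. Eligibility is 18–65 on every route, and the advertising is not confined to the campus where classes are held.
- *Self-referral as the fault.* Community poster respondents would be self-referred too, so this does not separate the two populations.
- *Loss of the justification for having no sample size calculation.* The reason given there is referral rates within the catchment area, which the GP and waiting-list routes still address.

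**Conclusion.** The point holds as a mismatch between the population named and the population sampled, with a stated inference resting on it. It is more than clerical, because participation by route is an explicit objective and recruitment data feed the planning of the main RCT. It should be corrected, but it does not threaten the validity of the trial.

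The scope is limited to one of three recruitment sources, and to the inference from that source to the general public. No numerical size can be attached. The GP and waiting-list routes, the target of 80 and the comparison of treatments are unaffected.

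The conclusion assumes that the text describes the route's reach completely, and that at least some main-trial centres would lack a comparable university population.

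**What to change.** Choose one of two changes:

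1. **Widen the route.** Extend the same posters and website to the community in the catchment area, and report those respondents separately from staff and students. The general-public claim can then stand on the community respondents.
2. **Narrow the claim.** In the Participants and Sample size sections, rename the route *university staff and students*, and drop the statements that it tests general-public recruitment or supplies a general-public rate. Keep the claim that it pilots advertised self-referral with GP confirmation.

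With either choice, state in Statistical methods that monthly recruitment and the ratio of screened to enrolled will be shown by route, as the Sample size section already implies. If the route is not widened, do not carry the campus rate into the projection for centres without a comparable university population. If it is widened, the community rate can be used in the projection alongside the GP and waiting-list rates.

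The first choice costs a little extra advertising. The second costs a wording change, a narrower claim and possibly a lower projected recruitment rate. The by-route table should need no new data, since rates by source are already promised.

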**Figure 1 F1:**
[figure not shown]
Recruitment of participants and flow through trial.

### Interventions

#### Personalised and supervised Exercise Programme (PEP)

##### Baseline Assessment and Goal Setting

Prior to the start of the PEP, each participant will attend the University's Health and Rehabilitation Sciences Research Institute (Jordanstown campus) for a baseline assessment (week 1, Figure 1). This will consist of: an individual consultation with one of two chartered physiotherapists (to discuss the content and aims of the PEP); an assessment of the participant's current level of activity, exercise capabilities and perceived barriers to recovery; recording of the participant's treatment expectations, and any previous CAM treatment; a brief lumbar spine assessment to rule out specific LBP (see Table 1 for exclusion criteria for radicular pain) [21,22]; discussion and agreement, between the therapist and the participant, on short and long-term treatment goals. The aim of agreeing such goals is to gradually include activities or postures which the participant has been avoiding because of their LBP, as well increasing their general activity/exercise levels. Each participant will be asked to document their agreed short term and long term goals in their logbook and the exercise class Record Card. The physiotherapist will emphasise to the participants that the supervised PEP classes are a stepping-stone to self directed activity and will emphasise some of key messages from the Back Book (see below) on how to self manage their back pain.

